**HYPOTHESIS**

1. The efficiency of the management of the SAHS using a work based on TIC's will be optimal to the one currently used in the hospital framework that uses both respiratory polygraph or PSG, including all types of patients from high probability to the most complex.
2. -The cost-effectiveness of the management of SAHS using a work based on ICT's is optimal than that currently used in the hospital framework that uses both respiratory polygraph or PSG, including all types of patients from high probability to the most complex.
3. -Optimal cost-effectiveness will occur especially in complex patients. These patients will directly contact the reference centre which, through the use of ICT, will simplify the process. These same groups of patients when they follow the usual process require several visits at different levels of care and always end up being diagnosed in the referral centers.
4. -The transfer of the telematic process will be possible and can be quickly included in the care routine.

**OBJECTIVES**

1. -Evaluation of two SAHS management programs, the classic one currently used as opposed to another based on work using ICT's taking the Quebec questionnaire as the main variable and in cases with CPAP the compliance of the treatment.

2. -Analysis of the cost-effectiveness of the programs mentioned above, valuing the Quebec questionnaire as the main variable and, in the cases of CPAP, compliance with treatment.

-Effectiveness of the program based fundamentally on technology between the group of complex patients (Groups 2 and 3 initially described) and the high possibility of suffering from an SAHS (Group 1). Questionnaires: Epworth and EuroQol-5D. Number of complications or side effects. 3. Patient satisfaction questionnaires

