Currently the majority of patients are followed in the reference centers (Figure 2-A) and obviously in the current context is not logical. Non-complex patients will be managed outside the hospital (Figure 2-B). However, complex cases, such as poor compliance, morbid obesity, surgical treatments, Cheyne Stokes, servoventilation, advanced age or severe associated pathologies, among others, should be treated in sleep units, and it is to be expected that in the future their number may increase significantly (Figure 2-C) and hence that hospital professionals should adapt to this changing reality and develop systems to care for this type of patients, ideally outside the hospital setting to optimize cost effectiveness. ICTs are an option since they allow the use of: a) appropriate diagnostic techniques (out-of-hospital PSG), b) studies of several days as we have recently published -type Holter-) (16) and c) teleconsultations (Figure 1). All of this is managed by sleep specialists (16) as we have verified that it is a very important option as it facilitates consultations that require less time, avoids trips for patients (loss of working hours or their distant residence or their condition prevents them from moving easily). In addition, occasional visits will improve compliance (15).

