**DESIGN**

DESIGN AND SUBJECTS OF THE STUDY (see figures at the end).

A randomized, open-ended, parallel patient group study in which an analysis of treatment efficacy and cost-effectiveness will be performed. All patients with suspected SAHS diagnosis who belong to the primary care centers (CAP) of the Esquerra del Eixample area of Barcelona, which corresponds to the health area of the Hospital Clínic of Barcelona, will be included consecutively. Patients with: a) psycho-physical incapacity to carry out questionnaires; b) difficulty in using communications technology (smartphone), c) pregnancy, d) failure to obtain informed consent, e) severe or disabling drowsiness or f) unstable illnesses will be excluded. Patients will be randomized, following a sequence generated by a database, into two groups (Table 1):

- Group 1: Patients who follow the usual procedure (hospital). After the visit in the primary physician/specialist out-of-hospital who will make a decisions. Can refer or not the patients to the hospital for a sleep test, titration if appropriate and follow-up for 6-12 months in the hospital (SEPAR regulations).
- Group 2: Telemedicine monitoring by the referral centre: this group of patients will be detected in the outpatient clinic in the same way as group 1 but will carry out the diagnosis, education, treatment and monitoring by means of a totally out-of-hospital telematic procedure carried out by sleep doctors. To minimize possible information biases derived from the open procedure, the professional in charge of introducing and evaluating the questionnaires as well as other main objective variables (measurement of CPAP compliance) will not know the patient's group of belonging.

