**Effectiveness assessment.**

Statistical analysis shall be based on the intention-to-treat principle. The comparison in the changes in the score of the QUEBEC questionnaire (6 months vs. Basal) between both groups will be carried out from the ANCOVA test, obtaining the mean scores at 6 months for each group adjusted by the basal values and other confusing variables such as the BMI, age or the severity of the SAHS. This test will be performed under the assumption of "least squares". Sub-analysis will be performed with the most complex patients in which the same analysis will be replicated. An analysis per protocol will also be carried out in the case of patients with CPAP depending on whether the compliance is less than or not at 4 h/night. For patients without the last follow-up visit, and therefore only with baseline information, the same baseline value will be imputed to the 24-week visit as it is the most conservative option and against the hypothesis of the potential benefit of CPAP intervention. A significant difference of <0.05 will be established for all tests (SPSS version 20 will be used).

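### CPAP compliance is named a main variable although it exists only in patients put on CPAP after randomisation, so its between-arm comparison is not a randomised one

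*Protocol*

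**What the plan says.** **Status of compliance.** Objective 1 evaluates the two programmes "taking the Quebec questionnaire as the main variable and in cases with CPAP the compliance of the treatment". Objective 2, on cost-effectiveness, repeats the pair, "valuing the Quebec questionnaire as the main variable and, in the cases of CPAP, compliance with treatment". The Summary also sets compliance beside Quebec. The Design section, describing the blinded assessor, counts it among the "other main objective variables (measurement of CPAP compliance").

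**Point of randomisation.** The Design section includes "All patients with suspected SAHS diagnosis who belong to the primary care centers (CAP") of one health area. Randomisation therefore comes before diagnosis and before any decision on CPAP.

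**Who decides afterwards.** In Group 1 the out-of-hospital physician or specialist decides: "Can refer or not the patients to the hospital for a sleep test, titration if appropriate". Patients in Group 2 "will carry out the diagnosis, education, treatment and monitoring by means of a totally out-of-hospital telematic procedure carried out by sleep doctors".

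**Recording and analysis.** The Variables section collects compliance only where CPAP is used. The Summary plans a plain between-arm comparison for it: difference in means, a nonparametric equivalent, or chi-squared. The Effectiveness assessment section declares intention to treat, describes an ANCOVA for Quebec, and adds that an "analysis per protocol will also be carried out in the case of patients with CPAP depending on whether the compliance is less than" 4 h/night or not.

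**Sections that differ.** The sample-size justification names the Quebec change as the main study variable and sizes the trial on it alone. The Cost-effectiveness section calls Quebec the main variable, with Epworth and EuroQol-5D as secondary effects, and does not mention compliance.

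**The concern.** Randomisation balances everyone who enters the trial. It does not balance the subgroup that later receives CPAP when the route to CPAP is part of what is being compared. If one pathway treats a wider or different range of patients than the other, hours of use among the treated can differ with no programme effect on adherence at all. They can also fail to differ when there is an effect.

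The split at 4 h/night adds a second layer of selection. In its argument for ICT, the Introduction says: "In addition, occasional visits will improve compliance". If the programme moves marginal users above 4 h/night, the adherent group in the telematic arm contains patients who would have been below the threshold under usual care. The adherent groups of the two arms are then different kinds of patient.

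What is at stake is the claim on compliance. As written, a non-randomised contrast would be reported as a main result of a randomised trial, alongside Quebec.

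**Working it through.** **1. The plan's own figure.** The only sample-size figure is 101 per arm, for a 2-point Quebec difference with alpha 0.05 and beta 0.20. No SD is stated, so it can be neither reproduced nor refuted. Solving backwards, two-sided, SD = 2 × √(n/2) / (1.960 + 0.842):
- n = 101 evaluable: 2 × 7.106 / 2.802 = 5.07 points.
- n = 101 already including 20% loss, so about 81 evaluable: about 4.54 points.

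Neither concerns compliance. The plan gives no sizing for it.

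**2. Order of events, read across sections.** Suspicion of SAHS → randomisation (Design) → decision on test and CPAP by arm-specific clinicians (Design) → compliance recorded if CPAP is used (Variables) → between-arm comparison of compliance (Summary). The set being compared is fixed two steps after randomisation. No section gives compliance a value for patients without CPAP. The imputation rule in the Effectiveness assessment section carries a baseline value forward, and no patient has a CPAP baseline before randomisation. The ANCOVA adjustment for severity is specified for Quebec only.

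**3. How large could the bias be?** Every input here is assumed, because the protocol gives no CPAP share, no SD of hours and no correlation. Suppose there is no true programme effect. Let a latent propensity to be put on CPAP correlate ρ with hours of use, and let each arm treat the top share q of that propensity. The mean shift among the treated is ρ × SD × λ(q), with λ(q) = φ(z)/q. The spurious difference is ρ × SD × [λ(q₁) − λ(q₂)].

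λ(0.50) = 0.798, λ(0.65) = 0.570, λ(0.80) = 0.350. With SD 2.2 h/night:

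| CPAP shares | λ difference | ρ = 0.3 | ρ = 0.5 |
|---|---|---|---|
| 50% vs 65% | 0.228 | 0.15 h | 0.25 h |
| 50% vs 80% | 0.448 | 0.30 h | 0.49 h |

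**4. Compared with sampling error.** With 101 randomised per arm, the standard error for 50% vs 65% is 2.2 × √(1/50.5 + 1/65.65) = 0.41 h, so the bias is about 0.4 to 0.6 standard errors. For 50% vs 80% it is 2.2 × √(1/50.5 + 1/80.8) = 0.39 h, giving about 0.7 to 1.2 standard errors.

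**5. Second set of assumptions, by simulation.** SD 2 h/night; severity correlated 0.2 to 0.5 with hours and 0.7 with the CPAP decision; no true effect.

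| CPAP shares | Spurious difference (h/night) | Type I error |
|---|---|---|
| 60% vs 60%, same rule | 0.00 | 5.0% |
| 60% vs 70% | 0.04 to 0.10 | 5.2% to 6.0% |
| 50% vs 70% | 0.09 to 0.21 | 5.6% to 8.8% |
| 40% vs 70% | 0.13 to 0.33 | 6.3% to 13.3% |

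**6. Precision.** If 40% to 80% of each arm is put on CPAP (assumed), the comparison has about 40 to 81 patients per arm. The standardised difference detectable with 80% power, 2.802 × √(2/n), is then 0.63 to 0.44, against 0.39 with all 101.

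**The case against.** The strongest reply is that compliance is already secondary in practice. The trial is sized on Quebec alone, Quebec has the only fully described model, and the Summary's statistics text places compliance among the other variables. This largely stands, and it makes the repair mainly one of wording. It does not remove the point: both objectives, the Summary and the Design section still give compliance main status, and the paragraph on secondary objectives does not list it.

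Second, both arms work to common standards. The Proceedings section applies the same AASM and SEPAR regulations to hospital and home studies, and SEPAR regulations to treatment. The Introduction reports that general pneumologists request tests appropriately, and Hypothesis 3 says complex patients in usual care always end up diagnosed at referral centres. This makes a large gap in CPAP share less plausible. It does not exclude one, because the Group 1 referral decision precedes those standards.

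Third, the assessor of compliance is blinded. That limits information bias but not selection.

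Fourth, the 4 h/night analysis is additional, and restricting it to CPAP patients is its stated scope. That stands. Per-protocol analyses select after randomisation by nature, so its presence is not an error. A reader might infer that it could hide or create the trial's Quebec difference. It cannot, because the main Quebec analysis covers all randomised patients. The sentence does not say whether arms are compared within adherence groups or adherent patients are compared with non-adherent ones; neither reading is randomised.

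A reader might also infer that one arm will treat milder or less motivated patients. Nothing in the document supports a direction.

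**Conclusion.** The point holds in a limited form. The protocol makes CPAP compliance a main variable while defining it only in patients who reach CPAP after randomisation through arm-specific decisions. That comparison lacks the protection of randomisation, and its status contradicts the sample-size and cost-effectiveness sections. The 4 h/night analysis selects further and can only be supportive. This conclusion follows from the text and needs no assumed number.

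The size of the bias does rest on assumptions. With CPAP shares 15 to 30 percentage points apart and the correlations above, it is about 0.1 to 0.5 h/night. With closer shares it is smaller, and it vanishes when both arms treat the same share by the same rule. These figures show what is possible, not what to expect. The Quebec intention-to-treat result is untouched.

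**What to change.** - In the Summary, Objectives and Design sections, state Quebec in all randomised patients as the sole main variable, in line with the sample-size and cost-effectiveness sections.
- Make compliance a secondary outcome. Label the CPAP-only comparison and the 4 h/night analysis as non-randomised and supportive, and say which groups the 4 h/night analysis compares.
- Report the number and proportion put on CPAP in each arm, with their baseline characteristics, so that readers can judge how far the two treated groups differ.
- Optionally add, as a sensitivity measure, the proportion of all randomised patients using CPAP at least 4 h/night. This keeps the randomised comparison but mixes prescription with use: a patient found not to need CPAP counts the same as one who gave it up, and an arm that prescribes more can look better. For that reason it should not replace the CPAP-only figures as the preferred measure.

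Redefining per-protocol as having followed the assigned pathway would not help, since it also selects on behaviour after randomisation.

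The cost is some rewording, one extra table and a weaker claim on compliance. Data collection and patient care do not change.

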**DESIGN**

DESIGN AND SUBJECTS OF THE STUDY (see figures at the end).

A randomized, open-ended, parallel patient group study in which an analysis of treatment efficacy and cost-effectiveness will be performed. All patients with suspected SAHS diagnosis who belong to the primary care centers (CAP) of the Esquerra del Eixample area of Barcelona, which corresponds to the health area of the Hospital Clínic of Barcelona, will be included consecutively. Patients with: a) psycho-physical incapacity to carry out questionnaires; b) difficulty in using communications technology (smartphone), c) pregnancy, d) failure to obtain informed consent, e) severe or disabling drowsiness or f) unstable illnesses will be excluded. Patients will be randomized, following a sequence generated by a database, into two groups (Table 1):

- Group 1: Patients who follow the usual procedure (hospital). After the visit in the primary physician/specialist out-of-hospital who will make a decisions. Can refer or not the patients to the hospital for a sleep test, titration if appropriate and follow-up for 6-12 months in the hospital (SEPAR regulations).
- Group 2: Telemedicine monitoring by the referral centre: this group of patients will be detected in the outpatient clinic in the same way as group 1 but will carry out the diagnosis, education, treatment and monitoring by means of a totally out-of-hospital telematic procedure carried out by sleep doctors. To minimize possible information biases derived from the open procedure, the professional in charge of introducing and evaluating the questionnaires as well as other main objective variables (measurement of CPAP compliance) will not know the patient's group of belonging.

**WORKING SCHEME:**

**Variables**

The following data shall be collected on patients who have passed the inclusion/exclusion criteria:

1) Anthropometric and clinical data related to SAHS. Symptoms related to other sleep disorders. Physical examination specifically maxillofacial ENT. Blood pressure. 2) Compliance with treatment if CPAP is used (meter reading and optimal pressure time).

Given the characteristics of the project and with the aim of simplifying the protocol which, due to its characteristics, must be simple, only a few additional variables will be collected, specifically:

- Quebec questionnaire (Lacasse and Thorax 2004), Spanish translationMedicina Clinica Merrejon 2012).
- EuroQol-5D (Eurocold group; health Policy 1990).
- Epworth sleepiness scale (Johns MW Sleep 1991) and
- Satisfaction scale and side effects. (Self-administered with 15 minutes of time for completion)

**Proceedings:**

Sleep studies and CPAP titration. 1) PSG or hospital respiratory polygraph (PR): The technique and analysis will be carried out according to AASM 2012-SEPAR 2011 regulations. 2) PSG or PR home. The technique and analysis will also conform to the aforementioned standardized regulations. The home care nursing group for chronic patients will also deliver the equipment. In this case the data will be transmitted to the hospital via telematics. For CPAP titration the same procedure will be followed except that the company will provide the automatic equipment for titration, the training will be done from the hospital via telematics and if it is a difficult titration will be adjusted for several days according to results observed telematrically. In the usual treatment arm the professionals of the traditional centres will follow the already established processes. Valid studies for PSG or PR will be considered those that comply with the regulations of the Spanish sleep group. As far as treatment is concerned, the SEPAR regulations will be followed (Lloberes et al. 2011).

Follow-up: Patients will be evaluated according to SEPAR general regulations (onset, at 1, 3 months, and 6 months) and above all depending on the medical criteria. Obviously the extra visits made will be valued. The aforementioned questionnaires will be collected and, in the case of CPAP, compliance at the beginning and at the end (CPAP compliance is not collected in the intermediate months because a group is telematic).

**Justification of sample size.** The main study variable is the change in the score of the dimension of the Quebec questionnaire that requires a higher "n". It is estimated that for an alpha error of 0.05, beta of 0.20 and a clinically relevant difference (change in total score ≥2 points on the questionnaire) between the two study groups, a minimum of 101 patients per randomization arm (202 patients in total) is required. An estimated 20% loss (between those who lose and those who do not tolerate CPAP), according to published data on the degree of compliance with CPAP in Spain is estimated at 75-80%.

**Statistics:**

Main objectives: After a filtering of the data collected, the variables of the study will be tabulated in a database. A specific unique code will be assigned to identify the patients. The connection key between the code and the subject will be in the hands of the IP who will assume all responsibility for data protection and care. The construction of the database, evaluation of questionnaires, entry of data into the database and analysis of the results will be carried out by personnel external to the research. The construction of the database and analysis of the data will be carried out by computer professionals and statisticians respectively. Univariate study: In the case of qualitative variables, their frequency and valid percentage will be determined. The lost values will be taken into account in order to give the results. For quantitative variables, measures of central tendency, position and dispersion will be included.

**Effectiveness assessment.**

Statistical analysis shall be based on the intention-to-treat principle. The comparison in the changes in the score of the QUEBEC questionnaire (6 months vs. Basal) between both groups will be carried out from the ANCOVA test, obtaining the mean scores at 6 months for each group adjusted by the basal values and other confusing variables such as the BMI, age or the severity of the SAHS. This test will be performed under the assumption of "least squares". Sub-analysis will be performed with the most complex patients in which the same analysis will be replicated. An analysis per protocol will also be carried out in the case of patients with CPAP depending on whether the compliance is less than or not at 4 h/night. For patients without the last follow-up visit, and therefore only with baseline information, the same baseline value will be imputed to the 24-week visit as it is the most conservative option and against the hypothesis of the potential benefit of CPAP intervention. A significant difference of <0.05 will be established for all tests (SPSS version 20 will be used).

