Secondary objectives: Comparison between both arms of the cited questionnaires (Epworth, EuroQol-5D, Satisfaction and number of side effects). In addition to having other variables of interest collected from each patient, these variables may act as covariates that help minimize uncertainty in the estimation of effectiveness and incremental cost. We therefore propose a series of secondary objectives linked to the proposed Bayesian methodology: 1) to develop a cost-effectiveness for more than one measure of effectiveness, also proposing clear decision-making measures that are easy to interpret and 2) to develop a BMA model (Bayesian Model Averaging) for estimating cost-effectiveness. The BMA solution is obtained as an average of the coefficients obtained by all the possible combinations of the covariates weighted by the a posteriori probability of each model. This implies the selection of which variables have predictive capacity since the choice of a single model among all the possible ones does not consider the uncertainty associated with the choice of the correct model. This objective will allow us to innovate this type of study since we will automatically select the relevant variables by means of the Bayesian selection of covariates (17).

Logistics: a) Protocol: based on the present memory; b) Procedure notebook: explains step by step the development of the study and contains all the questionnaires, tests and how to carry them out for standardization, c) Data collection notebook containing the variables to be collected distributed in the visits. The order and form is the same as that of the database; d) Database with domain belonging to the requesting centre.

Ethical aspects: The study will be carried out in accordance with the guidelines and principles of the Declaration of Helsinki and will be approved by the Ethics and Clinical Research Committee. All study subjects will provide informed consent in writing prior to participation. The quality assurance procedure will be permanent (data management, data security procedures are sufficient, effective and well documented).

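### The primary ANCOVA names SAHS severity as a covariate, but sleep-study severity is known only after allocation and through arm-specific testing, so adjusting for it can bias the comparison and drop randomised patients

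*Protocol*

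**What the plan says.** The protocol's Design section includes consecutive patients from the area's primary care centres in whom SAHS is suspected, and randomises them to two management pathways.

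- **Group 1 (usual procedure).** After the out-of-hospital visit, the physician decides: "Can refer or not the patients to the hospital for a sleep test, titration if appropriate".
- **Group 2 (telemedicine).** Patients "will carry out the diagnosis, education, treatment and monitoring by means of a totally out-of-hospital telematic procedure".

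The Proceedings section describes hospital and home sleep studies and leaves the usual arm to its established local processes.

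The Effectiveness assessment section opens with the principle: "Statistical analysis shall be based on the intention-to-treat principle". It then specifies the primary comparison, an ANCOVA of the Quebec score at 6 months, "adjusted by the basal values and other confusing variables such as the BMI, age or the severity of the SAHS", fitted by least squares. Its only imputation rule carries the baseline Quebec score forward when the last visit is missing.

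The secondary objectives paragraph, at the end of the Cost-effectiveness section, proposes Bayesian model averaging over covariates and says that "these variables may act as covariates that help minimize uncertainty in the estimation of effectiveness and incremental cost".

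**The concern.** Covariate adjustment in a randomised trial is safe when the covariate is fixed before allocation. Baseline Quebec, age and BMI meet that condition. Severity taken from a sleep study does not: the study is done after allocation, within the pathway being compared, and in Group 1 it may not be done at all.

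Two things are at stake for the primary endpoint:

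- If the two pathways give systematically different readings for the same patient, the ANCOVA corrects for a difference between arms that is not a difference between patients.
- If patients without a value leave the model, the comparison is no longer between the groups as randomised. If testing also depends on prognosis, those who remain are not comparable across arms.

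**Working it through.** **1. Is severity available before randomisation?** The Design section has patients entering on suspicion and places diagnosis inside the allocated pathway. The Variables section lists anthropometric data, clinical data related to SAHS, blood pressure, CPAP compliance and questionnaires. It names no severity score and no sleep study at entry. Severity is not defined anywhere. On the text as written, a value based on a sleep study can only follow allocation.

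**2. Is it obtained in the same way in both arms?** Group 2 is diagnosed "by means of a totally out-of-hospital telematic procedure carried out by sleep doctors". Group 1 follows local practice, and its physician may decide against referral. Setting, test mix and the choice of who is tested can all differ.

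**3. The plan's own figure.** The protocol states 101 per arm for a 2-point difference, alpha 0.05 and beta 0.20. It gives no SD, so 101 cannot be reproduced, only inverted. Two-sided, without loss:

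SD = 2 × √(101/2) / (1.960 + 0.842) = 14.21 / 2.802 = 5.07

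This SD is an inference, used below for illustration only.

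**4. Power if untested Group 1 patients are dropped.** Assume 10%, 20% or 30% of Group 1 are untested and all of Group 2 are tested. SE = 5.07 × √(1/101 + 1/n₁) and power = Φ(2/SE − 1.96).

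| Untested in Group 1 | n₁ | SE | Power |
|---|---|---|---|
| 0% | 101 | 0.713 | 0.80 |
| 10% | 90.9 | 0.733 | 0.78 |
| 20% | 80.8 | 0.757 | 0.75 |
| 30% | 70.7 | 0.786 | 0.72 |

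The loss of power is modest. Bias matters more.

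**5. Bias from a reading that differs by arm.** If the Group 2 reading is shifted by d SD and the outcome slope on severity is b points per SD, the adjusted estimate is about (true effect − b × d). With assumed b = 1.5 and true effect 2:

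- d = −0.2 gives 2 + 0.30 = 2.30
- d = −0.5 gives 2 + 0.75 = 2.75
- d = +0.5 gives 2 − 0.75 = 1.25

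**6. Simulation.** Settings: 101 per arm, true effect 2, outcome SD 5.07, b = 1.5, 3,000 runs per scenario. In the prognosis-dependent scenarios, the tendency to be tested has an assumed correlation of 0.5 in size with the outcome the patient would have without the effect. The severity-adjusted model is complete-case. The comparison model uses a baseline covariate only, in all randomised patients.

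| Scenario (assumed) | Severity-adjusted | Baseline covariate only |
|---|---|---|
| All tested, same measurement | 2.01 | 2.01 |
| 20% of Group 1 untested, at random | 1.99 | 1.99 |
| 20% untested, depending on true severity | 1.98 | 1.99 |
| Group 2 reading shifted −0.2 SD | 2.29 | 2.00 |
| Group 2 reading shifted −0.5 SD | 2.77 | 2.02 |
| Group 2 reading shifted +0.5 SD | 1.24 | 1.99 |
| 10% untested, poorer prognosis tested less often | 1.63 | 2.01 |
| 20% untested, same direction | 1.30 | 1.99 |
| 30% untested, same direction | 1.03 | 2.01 |
| 20% untested, opposite direction | 2.69 | 2.01 |

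The shift results agree with step 5. The baseline-only analysis stays between 1.99 and 2.02 throughout. The severity-adjusted analysis is unbiased in the first three rows and biased, in either direction, in the rest.

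**The case against.** **Bias is not inevitable.** A reader might infer that adjusting for severity necessarily biases the effect. The documents do not support that. With the same measurement in both arms, and testing that is random or depends only on severity, the simulation shows none. The diagnostic study also precedes CPAP, so the pathway can change the reading or its availability but not the disease at that point. The Proceedings section puts home and hospital studies under the same technical standards, and both settings use polysomnography or polygraphy. This makes a large shift less likely. It does not equalise setting, test mix or referral, so the risk stands.

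**Severity is undefined and only an example.** It stands in an open list, and a clinical grading recorded at entry would remove the problem. That is correct, but no such grading is described, and the list as written permits the post-allocation value.

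**The details may sit in an analysis plan that is not shown.** Handling of missing covariates can fairly be left there, so its absence is not the criticism. Loss of patients is conditional on complete-case fitting, the usual behaviour of least-squares ANCOVA. What the protocol does state is an unsuitable covariate for its primary model.

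**Telemedicine patients may also lack a value.** A reader might infer that only Group 1 loses patients. The protocol does not guarantee a valid study for everyone in Group 2, so one-sided loss is an assumption.

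**The model-averaging paragraph is ambiguous.** A reader might infer that outcome questionnaires are to enter as covariates. The sentence more naturally refers to other variables collected from each patient, and it concerns the cost-effectiveness model. It supports a precaution, no more.

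**Conclusion.** The point holds in conditional form and is worth correcting because it touches the primary analysis. The protocol names as a covariate a quantity that, on its own design, is known only after allocation, comes from arm-specific processes and may not exist for unreferred Group 1 patients. Adjusting for it can bias the estimate, and under complete-case fitting it removes randomised patients despite the intention-to-treat statement in the same section.

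Size and direction cannot be fixed from the documents. The range of 1.03 to 2.77 around a true effect of 2 shows what is possible. It rests on an assumed slope, assumed shifts, assumed shares untested and an SD inferred from the sample size. It is not a prediction for this trial.

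**What to change.** - **Primary ANCOVA.** Remove sleep-study severity. State that covariates are values recorded before randomisation: baseline Quebec, age, BMI and, if wanted, baseline Epworth. Add pre-test group only if it is recorded before allocation. The Introduction says patients are taken without assessing their initial characteristics, so this cannot be presumed.
- **Severity.** Define it, then report it by arm descriptively or use it in a labelled sensitivity analysis.
- **Model averaging.** As a precaution, limit the candidate covariates in the secondary objectives paragraph to variables measured before randomisation.

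The planned 101 per arm does not change. The cost is a change of wording and a small possible loss of precision, which baseline Epworth may partly recover. Recording pre-test group before allocation, if it is wanted, would be an added baseline step.
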